##### 2.4.2.1. Sensitivity analysis for missing data

We will compare demographic and clinical covariates in participants with and without missing data to identify factors potentially contributing to missingness. We will use 10 multiple imputations from the original dataset using the predictive mean matching method substituting missing values within each impute.

##### 2.4.2.2. Power: aim 1

To achieve 80% power to detect non-inferiority using a one-sided, two-sample *t*-test (lower bound), we will need 85 participants per group. The margin of non-inferiority is 5% of weight loss in the DPP-TOAT arm. The true efficacy difference between the 6-month weight loss is assumed to be 1.6 kg (weight loss of 5 kg in the V-DPP-TOAT arm and 6.6 kg in the in-person DPP-TOAT arm with standard deviation of 5 kg in each arm (42)). The significance level (alpha) of the test is 0.05. A total of 230 participants are needed, assuming 25% attrition at 6 months based on data from our work and others (22, 42, 43).

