#### 2.4.2. Aim 1: quantitative data analysis

We will compare the effect of the V-DPP-TOAT versus the DPP-TOAT interventions on weight and glycemia, which are both continuous outcomes. First, we will report means and standard deviations by randomization assignment and assess the assumption of normality in the outcomes. We will estimate the model using ordinary least squares regression
$$Y6_{i}=\beta_{0}+\alpha_{0}Y0_{i}+\alpha_{1}P_{i}+e_{i}$$
where 
$Y6_{i}$
 is the 6-month weight or Hemoglobin A1c for participant 
i
. 
$Y0_{i}$
 is the baseline weight or A1c for participant 
i
. 
$P_{i}$
 is an indicator variable, where 
$P_{i}=1$
 if the participant 
i
 has been randomized to V-DPP-TOAT, and 
$P_{i}=0$
 for the DPP-TOAT. 
$e_{i}$
 is an error term. The parameters to be estimated are as follows: 
$\beta_{0}$
 is the average for those in the DPP-TOAT group; 
$\alpha_{0}$
 represents the relationship between the baseline and follow-up outcome (weight or A1c) measurement; if the relationship is strong, the inclusion of the baseline measurement can increase statistical power; and 
$\alpha_{1}$
 represents the effect of the V-DPP-TOAT intervention. Specifically, the hypothesis test will compare 
$H_{0}:\alpha_{1}<\Delta$
 vs. 
$H_{A}:\alpha_{1}\geq -\Delta$
 with the noninferiority margin 
Δ
 set as 5% for each of the outcomes. We will calculate the 95% confidence interval of 
$\alpha_{1}$
. If the lower bound is above the margin -Δ, the V-DPP-TOAT is deemed non-inferior and the trial is a “success.” Further, if the lower bound of that same CI is also above zero, then superiority of V-DPP-TOAT can also be declared (41). Interaction terms between 
$Y0_{i}$
 and 
$P_{i}$
 will be tested to see if there is effect modification by any of the baseline covariates.

We will assess heterogeneity in outcomes among healthcare settings/clinics by estimating an intraclass correlation coefficient (ICC). If the heterogeneity cannot be ignored, we will use a multi-level model with nested random effects in the above equation to accommodate the correlations caused by healthcare settings/centers. Outcomes analysis will use an intention-to-treat principle, with a per-protocol analysis as a sensitivity analysis (41) employing R software (version 1.2.5019, R Foundation for Statistical Computing) for all analyses.

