##### 2.4.3.2. Quantitative data analysis

Aim 2 uses the RE-AIM framework to evaluate implementation of the V-DPP-TOAT and in-person DPP-TOAT interventions. We will compare the number of group sessions completed by each participant in the two arms using generalized linear models with count outcomes, because DPP session attendance is positively associated with weight loss (42, 46), and is a CDC recognition status benchmark (47). The proportion of participants who complete at least eight intervention sessions will be compared by logistic regression between the two arms to make our findings comparable to other DPP implementation studies (42, 46). However, our primary implementation outcome of attendance is independent of any threshold chosen in the number of sessions. We will test interaction terms between baseline covariates and treatment assignment to determine if there is effect modification by any of the baseline covariates.

If there are imbalances at baseline for any important participant health, demographic or other factors, we will adjust the models to take these imbalances into consideration. For the remaining analyses, we will conduct similar types of analyses, using logistic regression for categorical outcomes and linear regression models for continuous outcomes.

We will use mediation analysis to dissect the indirect effects of the treatment acting through the intermediate variables (social support, self-efficacy, and self-monitoring) on the primary outcome (attendance), and the direct effects of treatment on the outcome (attendance) not mediated through the mediators. For each of the three mediators, an overall score and subscale scores will be computed by summing relevant items. This analysis will help understand the underlying treatment mechanisms of behavior change. Specifically, we will use the principal stratification and structural mean models. We will assess the assumptions necessary for attaining identifiability of key parameters of the basic causal model and perform a series of sensitivity analyses. We will also investigate the interactions between baseline covariates and the mediation effects to determine whether any baseline factors modify the mediation effects (48, 49).

In order to inform cost for future implementations and policy makers (4), we will compare the sum of variable (e.g., operating costs, supply costs, percent time of intervention and staff) and fixed costs (e.g., space, equipment) between intervention arms (50).

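### The named missing-data sensitivity analysis assumes missing at random, as the primary regression does, so it does not test whether drop-outs did worse than similar completers

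*Protocol article*

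**What the plan says.** Section 2.4.2.1 of the protocol article, on sensitivity analysis for missing data, has two steps. The first is descriptive: "We will compare demographic and clinical covariates in participants with and without missing data to identify factors potentially contributing to missingness". The second is the imputation: "We will use 10 multiple imputations from the original dataset using the predictive mean matching method substituting missing values within each impute". It states no shift, tipping point or reference-based scenario, and it does not list the variables in the imputation model.

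Section 2.4.2 gives the primary analysis: "We will estimate the model using ordinary least squares regression". The 6-month value is regressed on the baseline value and arm. The same section names one other sensitivity analysis: "Outcomes analysis will use an intention-to-treat principle, with a per-protocol analysis as a sensitivity analysis". That one varies adherence, not what is assumed about unobserved weights.

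Three further statements bear on the point:

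- Section 2.4.2.2 (Power: aim 1): "A total of 230 participants are needed, assuming 25% attrition at 6 months based on data from our work and others".
- Section 2.4.2.2, on the margin: "The margin of non-inferiority is 5% of weight loss in the DPP-TOAT arm". Section 2.4.2 says only that it is "set as 5% for each of the outcomes", with no base for the percentage.
- Section 2.4.3.2 compares sessions completed by arm, "because DPP session attendance is positively associated with weight loss".

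**The concern.** Predictive mean matching gives a participant with no 6-month weight the observed weight of someone who returned and had a similar predicted value. Unless a shift is added, drop-outs are taken to have done as well as completers who look like them on the imputation variables. A regression on observed 6-month values makes the same kind of assumption, given baseline and arm. If it fails, both analyses can be wrong in the same direction, and their agreement would say little.

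The failure is plausible here. A quarter of participants are expected to be missing, and the plan itself links attendance to weight loss, so people who stop coming may have lost less than similar people who stayed. The margin in the power section is small, so a modest departure in one arm matters. What is at stake is whether a non-inferiority conclusion can be shown to withstand reasonable alternatives for the missing quarter.

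**Working it through.** **Inputs.** From section 2.4.2.2: assumed loss 6.6 kg in person and 5 kg virtual, SD 5 kg per arm, one-sided alpha 0.05, power 80%, 85 per group, 25% attrition, margin 5% of the in-person loss. From section 2.4.2: the decision uses the lower bound of a 95% confidence interval. From section 2.1: N = 230, 1:1, so 115 per arm.

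**The plan's own figure.** Margin = 0.05 x 6.6 = 0.33 kg. The normal-approximation size is n = 2 x 5² x (1.645 + 0.842)² / d².

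- With d = 0.33 + 1.6 = 1.93 kg, n = 83. The t-based version needs 84, and 85 gives 80.5% power. Attrition: 85/0.75 = 113.3, so 114 per arm or 228, stated as 230.
- This takes the 1.6 kg in the virtual arm's favour. In the stated direction d = 0.33 - 1.6 = -1.27 kg, and power at 85 per group is about 0.05%.
- A margin of 3.51 kg (5% of a 70.2 kg body weight, a weight the document does not give) with the 1.6 kg in the stated direction, d = 1.91 kg, also gives 85. The sample size therefore does not settle the margin's base. The 0.33 kg rests on the wording of section 2.4.2.2.

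**Shift in the arm difference.** Let p be the fraction missing and δ the amount by which drop-outs lost less than similar completers. The bias in the virtual-minus-in-person difference in loss is p(virtual) x δ(virtual) - p(in-person) x δ(in-person).

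With δ(in-person) = 0 and p(virtual) = 0.25, departures of 1, 2 and 3 kg give 0.25, 0.50 and 0.75 kg. The departure that moves the estimate by 0.33 kg is 0.33/p:

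| Missing in virtual arm | Departure |
|---|---|
| 15% | 2.20 kg |
| 20% | 1.65 kg |
| 25% | 1.32 kg |
| 30% | 1.10 kg |

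1.32 kg is 0.26 of the 5 kg SD. If p and δ are equal in the two arms, the bias is zero.

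**Do the planned analyses register it?** A simulation used 115 per arm, 25% missing, completers losing 5 kg on average in both arms, virtual drop-outs losing 1.32 kg less, and an assumed baseline weight of mean 90 kg, SD 15 kg. The true all-randomised difference is -0.33 kg. Complete-case regression gave -0.005 kg (Monte Carlo SE 0.005). Predictive mean matching on baseline and arm only gave 0.01 kg (SE 0.03). Neither registers the departure.

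**Effect on the decision.** With 85 per arm, SE = 5 x √(2/85) = 0.77 kg. If the true difference is -0.33 kg and the bias is 0.33 kg, the chance of declaring non-inferiority falsely rises from 2.5% to 1 - Φ(1.96 - 0.33/0.77) = 6.3% under the 95% interval rule. At one-sided 0.05 it rises from 5% to 11.2%.

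**Why 1.32 kg is not the tipping point.** The rule looks at the lower bound L, on the weight-loss scale. With the interval's width taken as unchanged, the virtual-only tipping departure is (L + 0.33)/0.25, which equals 1.32 kg only if L = 0. The half-width is 1.96 x 0.77 = 1.50 kg, so non-inferiority needs an estimate of at least 1.50 - 0.33 = 1.17 kg in the virtual arm's favour. Depending on L, the tipping departure could be near zero or well above 1.32 kg.

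**The case against.** The strongest reply is that multiple imputation by predictive mean matching is an accepted method, that the article is a condensed account, and that a tipping-point grid is the kind of detail a fuller plan may hold. A reader might infer that no missing-not-at-random analysis will ever be run. The article does not say so. What stands is narrower: the article does name its missing-data sensitivity analysis, and the one named does not vary the assumption in question.

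Next, the link between attendance and weight loss does not by itself show that data are missing not at random. Facilitators record attendance (section 2.4), weights are reported or measured around sessions (2.3.1.1 and 2.3.1.2), and smart scales transmit weights (2.3.1). If these enter the imputation, drop-outs would be matched to poorly attending completers, and much of the departure could be absorbed. A reader might therefore go too far in saying that the imputation would agree with the primary result whatever the drop-outs really weighed. That follows only if the imputation adds no predictors beyond baseline and arm, as in the simulation. The article does not say which predictors are used.

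Finally, a reader might infer that the bias favours the virtual arm. Section 2.4.3.3 expects 89% of virtual and 63% of in-person participants to complete at least eight sessions. If disengagement is heavier in person, in-person drop-outs could be the worse group and the net bias would work against non-inferiority. This objection stands in full: the direction is not established.

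**Conclusion.** The point holds as a cheap improvement worth making. The stated missing-data sensitivity analysis and the primary regression both assume missing at random, so the plan does not test whether drop-outs did worse than similar completers.

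The size is 1.32 kg in virtual-arm drop-outs for a 0.33 kg move in the estimate. It rests on three assumptions: 25% missing in the virtual arm, no departure among in-person drop-outs, and a margin of 0.33 kg. If the 5% meant body weight (not given; 70 to 100 kg assumed), the margin would be 3.5 to 5 kg and the corresponding departure 14 to 20 kg. Sections 2.4.2 and 2.4.2.2 must be reconciled on this. The structural gap does not depend on the margin.

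Two stronger readings are not supported: that 1.32 kg in drop-outs would overturn the conclusion, and that the planned imputation is lenient to the virtual arm. The small margin against a half-width of 1.50 kg, and the direction of the assumed 1.6 kg difference, are separate and larger matters.

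**What to change.** Keep the predictive mean matching and make these additions before outcomes are seen:

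1. State the imputation variables, and include recorded attendance and available session or smart-scale weights.
2. Add a delta-adjusted grid on the same imputed datasets that worsens imputed 6-month values by 0, 1, 2, ... kg. Vary the two arms separately, including a virtual-only row. Do the same for HbA1c in its own units.
3. Code the outcome so that a worse virtual result counts against the virtual arm, for example as weight loss. Section 2.4.2 models 6-month weight and declares non-inferiority when the lower bound exceeds -Δ. Read literally, adding kilograms to virtual drop-outs would make that rule easier to meet.
4. Apply the confidence-interval rule at each grid point, with one reconciled margin, and report the deltas at which the conclusion changes.

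The cost is a few lines of code and one more table, with no new data. The only downside is that a fragile result would be shown as fragile.

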## 2. Methods

### 2.1. Study design and overview

We will conduct a type 1 hybrid (14), randomized, controlled trial of the BRInging the Diabetes prevention program to GEriatric Populations (BRIDGE) study, which will compare an in-person DPP Tailored for Older AdulTs (DPP-TOAT) to a DPP-TOAT delivered via group virtual sessions (V-DPP-TOAT; Figure 1). All randomized individuals (*N* = 230; 1:1 randomization) will receive 22 intervention sessions over the course of a year facilitated by a certified DPP lifestyle coach, but the delivery method will vary (virtual versus in-person).

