### 2.3. Intervention arms

#### 2.3.1. Common components to both interventions: V-DPP-TOAT and DPP-TOAT

Both programs will be composed of sixteen 60-min weekly/bi-weekly sessions followed by six 60-min monthly support sessions (see Appendix B) with a group size of 8–15 facilitated by a certified DPP lifestyle coach. The DPP intervention is based on Social Cognitive Theory (20), which focuses on the role played by self-referent thought in the maintenance of behavior change. The following describes the theoretical concepts threaded throughout the intervention sessions. Self-efficacy (e.g., the participant’s confidence in their ability to engage in healthier behavior) is derived from four major sources of information: (1) mastery experiences; (2) social modeling; (3) verbal persuasion; and (4) physiological states. Mastery experiences emphasize past successes; setting incremental, easily achievable goals; identifying modifiable barriers to healthy behavior; receiving positive feedback on goal achievement; and practicing problem solving skills around barriers to adherence. Social modeling enhances mastery when participants share their successes and help each other problem-solve around barriers they encounter. Verbal persuasion emphasizes the participant’s previous successes to demonstrate their capability (e.g., “As a result of your effort, you lost a pound last week. You can do it again.”) We will assist participants in recognizing physiologic benefits they experience from lifestyle change (e.g., more energy, better sleep, or BP control). Intervention materials, which are based on the 2021 PreventT2 lifestyle change program (21), will include:*Participant Manual*: An evidence-based manual describing detailed program content and personalized calorie and macronutrient recommendations to achieve the desired weight. Written at the sixth-grade reading level in a large (14 point) sans serif font, self-assessments and goal setting procedures will be included along with approaches to self-monitor food intake, physical activity, and cooking and meal pattern guides. To enhance self-identification with the program and for ongoing visual cues for program affiliation, we will provide tote bags inscribed with the institutional logo.*Tailoring of content for aging*: Based on our prior work (22), we have adapted group sessions to the unique needs of older adults. Resources include healthful eating strategies for dentition issues, changes in taste, and special attention to interactions between food and medications. Physical activity sessions provide adaptations for physical limitations, including chair exercises and strength training.*Food Guide*: Resources developed by the United States Department of Agriculture (23) providing tailored advice for older adults will be provided, along with instructions and tips for using programs such as Healthwatch 360 (24) to track calorie and nutrient intake compared to recommendations.*Hearing Assistance*: For participants in the in-person arm, we will offer a personal amplifier (PA; PockeTalker™) to all participants to address any self-reported or suspected hearing loss. A simple PA consists of an amplifier and microphone with the amplifier feeding a speaker’s voice directly into the wearer’s ears via headphones or ear buds. These devices reduce the difficulty with hearing in “difficult listening situations” by feeding the speaker’s amplified voice directly into the patient’s ear, while headphones or ear buds muffle external sounds (i.e., signal is louder than background noise level). These devices require no professional customization; simple volume and tuning controls allow for use directly out of the box. PAs enhance communication for those who have hearing loss in a variety of clinical settings (25–27). PAs were equivalent in performance to hearing aids in one randomized controlled trial (28), sound quality of PAs was preferred over hearing aids, improved physician-patient communication for elderly hospitalized patients (29) and understanding discharge information in an Emergency Department setting (30). Participants in the virtual arm will be offered ear buds to address any self-reported or suspected hearing loss.*Videos*: Each intervention session will also feature educational and behavioral coaching videos developed by our team or reputable organizations such as the National Institutes Health and VA MOVE (Weight Management Program, supported by VA’s National Center for Health Promotion and Disease Prevention) (31). The videos last 3–5 min, and will be used to anchor the discussion. Videos will also be available on the study website for participants to review as they desire.*Smart Scales*: We will provide participants with a Renpho® (Joicom Corporation, Eastvale, CA) Smart Scale for Body Weight, Digital Bathroom Scale for self-monitoring purposes and to monitor weight given the possibility of disruptions in in-person study visits due to COVID-19 pandemic restrictions. Renpho® Scales will transmit weights to researchers automatically using BlueTooth technology and have been used in other weight management studies. A research assistant will instruct each participant during the baseline visit on using the scale to report weekly weights, providing written instructions as well as a phone number and email address to obtain technical support as needed.

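### Ten imputations leave avoidable random-seed noise, about 0.15 kg in the confidence bound without auxiliary predictors, in the missing-data sensitivity analysis; at least 100 would nearly remove it

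*Protocol article*

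**What the plan says.** Under the title "Sensitivity analysis for missing data" (section 2.4.2.1), the protocol article commits to a method and a count: "We will use 10 multiple imputations from the original dataset using the predictive mean matching method substituting missing values within each impute". It lists no imputation variables.

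The power section (2.4.2.2) supplies the figures that determine how much that count matters:

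- Sample size and attrition: "A total of 230 participants are needed, assuming 25% attrition at 6 months". Section 2.1 gives "1:1 randomization", so 115 per arm.
- Variability of 6-month weight loss: "with standard deviation of 5 kg in each arm".
- Margin: "The margin of non-inferiority is 5% of weight loss in the DPP-TOAT arm". The in-person loss is assumed to be 6.6 kg.

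Section 2.4.2 judges non-inferiority from the 95% confidence interval of the arm coefficient in an ordinary least squares model adjusted for baseline. Imputation is not mentioned there.

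Section 2.3.1 says of the home scales given to participants: "Renpho® Scales will transmit weights to researchers automatically using BlueTooth technology".

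**The concern.** Ten imputations are usually adequate for efficiency: the pooled standard error is barely larger than with many more. Reproducibility is a different matter. A multiply imputed estimate carries Monte Carlo error, and so does its confidence bound. Here the bound is compared with a fixed threshold to give a yes or no, a quarter of the outcomes are expected to be missing, and the margin is a fraction of a kilogram.

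The sensitivity analysis exists to show whether missing data change the conclusion. If its answer can change with the seed, a discordant result is hard to interpret: the reader cannot tell whether the missing data or the random draw produced it.

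**Working it through.** **Inputs.** SD 5 kg, 230 participants at 1:1 (115 per arm), 25% missing at 6 months, 10 imputations, 95% interval (multiplier 1.96), margin 5% × 6.6 = 0.33 kg. Assumptions of this check: the 5 kg serves as residual SD of the adjusted model, data are missing at random, and the imputation model holds only baseline weight and arm, so the fraction of missing information equals 25%.

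**Is 0.33 kg the plan's own margin?** The stated size is 85 per group. With one-sided alpha 0.05 and 80% power, n = 2 × 25 × (1.645 + 0.842)² / (0.33 + 1.6)² = 83 per group by the normal formula and 84 by the exact t calculation. Then 170 / 0.75 = 227, against 230 stated. So 0.33 kg is the margin behind the stated size. The match requires the 1.6 kg to count in favour of the virtual arm, whereas the text places it against that arm. That is a separate and larger problem, and the noise calculation below does not depend on it.

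**Seed noise at m = 10 (Rubin's rules).**

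- Within-imputation variance: W = 2 × 25 / 115 = 0.435.
- Total variance with unlimited imputations: 2 × 25 / 86.25 = 0.580, so B = 0.580 − 0.435 = 0.145.
- Pooled SE: √(0.435 + 1.1 × 0.145) = 0.771 kg.
- Monte Carlo SD of the estimate: √(B/m) = √0.0145 = 0.120 kg.
- Monte Carlo SD of the SE: (1 + 1/m) × B × √(2/(m − 1)) / (2 × SE) = 1.1 × 0.145 × 0.471 / 1.542 = 0.049 kg.
- Monte Carlo SD of the bound: √(0.120² + (1.96 × 0.049)²) = 0.154 kg. This is 47% of the margin and 20% of the pooled SE.

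Simulated predictive mean matching on fixed data sets of 230, with 29 missing per arm, gave 0.111 kg for the estimate and 0.146 kg for the bound.

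**Range over assumptions and over m (SD of the bound).**

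| Setting | kg |
|---|---|
| m = 10, residual SD 3 / 4 / 6 kg | 0.092 / 0.123 / 0.184 |
| m = 10, SD 5 kg, auxiliaries explain 25% / 50% / 75% of residual variance | 0.128 / 0.099 / 0.066 |
| SD 5 kg, no auxiliaries, m = 20 / 50 / 100 | 0.106 / 0.066 / 0.047 |

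**How often would two seeds disagree?** Let d be the true difference in weight loss, virtual minus in-person. The bound averaged over seeds is roughly normal with mean d − 1.96 × 0.771 = d − 1.51 and SD 0.771. Two runs disagree when their bounds fall on opposite sides of −0.33. Approximately, P = (2/√π) × s × f = 1.128 × s × f, where s is the seed SD of the bound and f is that normal density at −0.33. For d = 0 and m = 10: z = (1.51 − 0.33)/0.771 = 1.53, f = 0.160, and P = 1.128 × 0.154 × 0.160 = 2.8%. Numerical integration gives:

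| True difference (kg) | m = 10 | m = 100 |
|---|---|---|
| −1.6 (as stated in the power section) | 0.02% | under 0.01% |
| −0.33 (at the margin) | 1.4% | 0.4% |
| 0 (equal arms) | 2.8% | 0.9% |
| +0.8 | 7.8% | 2.4% |
| +1.18 (mean bound on the threshold at m = 10, worst case) | 8.8% | 2.7% |
| +1.6 | 7.7% | 2.3% |

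**The case against.** The strongest case against rests on four points.

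- **Role.** The imputation is a sensitivity analysis, and success is defined from the regression model. A reader might infer that the trial's verdict hangs on a seed. The text does not support that, and this point stands in full.
- **Yardstick.** Dividing 0.15 kg by a 0.33 kg margin makes the noise look decisive, and a reader might infer that the conclusion is unstable. What matters is how often the bound lands close to the threshold, and that depends on the pooled SE of 0.77 kg, five times the noise. Disagreement is therefore uncommon, and the 8 to 9% figures need a true benefit of the virtual arm, opposite in direction to the stated planning assumption. The margin also needs reconciling, since section 2.4.2 gives 5% without a base. A different margin would change the 47%, though not the 0.15 kg.
- **Auxiliary data.** The 0.15 kg assumes none, while the article lists no imputation variables at all. Good predictors could halve it. This stands, and the figure must carry that condition.
- **Level of detail.** A reader might count the missing seed and the silence on scale weights as defects. An article commonly leaves such detail to the full protocol or analysis plan, so neither is a finding. It is also undocumented how well scale weights would predict a missing clinic weight, since people who leave the study may stop weighing themselves.

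What survives is that the count of ten is stated, not omitted, and that a larger count is better at almost no cost.

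**Conclusion.** The point holds as a minor, nearly free improvement. At the plan's own SD, sample size and attrition, ten imputations leave a seed SD of about 0.15 kg in the 95% bound if only baseline weight and arm are used, and about 0.07 to 0.13 kg with useful auxiliary predictors. The effect is confined to the robustness check, where it would make two seeds disagree in anything from almost no trials to 8 to 9% of them, and in about 3% if the arms are equal. The calculation assumes data missing at random, a residual SD of 5 kg and a margin of 0.33 kg.

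**What to change.** In section 2.4.2.1, replace 10 with at least 100 imputations and state that the seed is set in advance and recorded. Under the assumptions above, the seed SD of the bound falls from about 0.15 to about 0.05 kg. The chance that two seeds disagree falls from 2.8% to 0.9% with equal arms, and stays below 3% in the worst case.

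Optionally, name the transmitted smart-scale weights as auxiliary predictors alongside arm and baseline covariates. They are already planned for collection in both arms.

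The cost is one line of text and minutes of computing. No new data are needed and the sample size is unchanged.

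### The Aim 1 sample size is set at one-sided alpha 0.05, but non-inferiority is decided on a 95% confidence bound (conventionally one-sided 0.025); a design with 80% power at the first level has about 70% at the second

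*Protocol article*

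**What the plan says.** Protocol article, section 2.4.2.2 (Power: aim 1), introduces the sizing test with the words "To achieve 80% power to detect non-inferiority using a one-sided, two-sample" and names Student's test as the method. The resulting requirement is put as "we will need 85 participants per group". On the error rate the paragraph adds: "The significance level (alpha) of the test is 0.05". Taken together, that is one-sided 0.05. The same paragraph gives the other inputs. For the margin it says: "The margin of non-inferiority is 5% of weight loss in the DPP-TOAT arm". For the planning assumption about the two arms, it says: "The true efficacy difference between the 6-month weight loss is assumed to be 1.6 kg", which comes from losses of 5 kg (virtual) and 6.6 kg (in person). The spread is given as "with standard deviation of 5 kg in each arm".

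Section 2.4.2 (Aim 1: quantitative data analysis) gives the decision rule. It begins "We will calculate the 95% confidence interval of" the treatment coefficient. Non-inferiority is declared if the lower bound lies above minus the margin, and superiority may also be declared if the lower bound of that same interval is above zero. The section does not say whether the interval is one- or two-sided.

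**The concern.** The trial is sized for one test and judged by another. One-sided 0.05 corresponds to a bound of a two-sided 90% interval, whereas a bound of a two-sided 95% interval is a one-sided 0.025 test. If 85 per arm gives 80% power at the looser level, it gives less at the stricter one, and the stated power of the primary effectiveness comparison is too high.

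There is also a problem of interpretation. A result whose 90% interval clears the margin but whose 95% interval does not would be non-inferior under the test in the power paragraph and not under the rule in the analysis section. The error rate of the primary conclusion should not be open to that choice once data are in.

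**Working it through.** **Inputs.** From section 2.4.2.2: 85 evaluable per arm, SD 5 kg, 80% power, one-sided alpha 0.05, margin 5% of the in-person weight loss, assumed losses 5 and 6.6 kg, attrition 25%. From section 2.1: "1:1 randomization", N = 230. From section 2.4.2: decision on a 95% interval bound, taken as two-sided (an assumption).

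**Formula.** With d the distance between the assumed truth and the margin, SE = SD × √(2/n) = 5 × √(2/85) = 0.767 kg, and power ≈ Φ(d/SE − z), where z = 1.645 at one-sided 0.05 and 1.960 at one-sided 0.025. Figures marked t use the noncentral t distribution.

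**1. Reproducing 85 per arm from the stated inputs.** The margin is 0.05 × 6.6 = 0.33 kg and the virtual arm is assumed 1.6 kg worse, so d = 0.33 − 1.6 = −1.27 kg. The assumed truth is already beyond the margin, and no sample size gives 80% power. With 85 per arm, power is Φ(−1.656 − 1.645) ≈ 0.0005 at one-sided 0.05 and about 0.00015 at 0.025. The figure of 85 is not reproduced.

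**2. What distance does give 85 per arm?** At one-sided 0.05, d = 0.767 × (1.645 + 0.842) = 1.907 kg (normal), or 1.915 kg (t). Two readings come close:
- the sign of the 1.6 kg reversed: d = 0.33 + 1.6 = 1.93 kg, needing 83 (normal) or 84 (t) per arm;
- a margin of 3.5 kg, which is 5% of an assumed 70 kg body weight not given in the article: d = 3.5 − 1.6 = 1.90 kg, needing 86 or 87.

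The attrition step is consistent: 85/0.75 gives 114 per arm, 228 in total, against 230.

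**3. The same designs under the 95% interval rule.**

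| d (kg) | Power at 85/arm, one-sided 0.05 (t) | Power at 85/arm, one-sided 0.025 (t) | n/arm for 80% at 0.025 (t) |
|---|---|---|---|
| 1.90 | 79.5% | 69.3% | 110 |
| 1.915 | 80.0% | 69.9% | 108 |
| 1.93 | 80.5% | 70.6% | 107 |

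The normal approximation gives 69.8% and 71.1% for the first and last rows. In general, a design with exactly 80% power at one-sided 0.05 has Φ(1.645 + 0.842 − 1.960) = Φ(0.527) ≈ 70% at one-sided 0.025. Type II error goes from 20% to about 30%.

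**4. Size of the shortfall.** With 25% attrition, 107 per arm is 143 randomized per arm (286 in total), and 110 is 147 (294 in total), against 230 planned.

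**5. Baseline adjustment.** The analysis model includes baseline weight. If the 5 kg is the SD of change and the variances at the two visits are equal, the residual SD is 5 × √((1 + ρ)/2), where ρ is the correlation between baseline and 6-month weight. The article gives no ρ. At an assumed 0.9 the SD is 4.87 kg and power at d = 1.915 is about 72%; at 0.8 it is 4.74 kg and about 74%. Neither closes the gap.

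**The case against.** Four points can be made against this.

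First, section 2.4.2 never prints the word two-sided, and the power paragraph speaks of a one-sided test on the lower bound. A one-sided 95% bound would remove the mismatch. This limits certainty and is a reason to ask for the sidedness to be stated. It is the less natural reading, because the text speaks of a confidence interval and takes superiority from the same one. On the one-sided reading, superiority would be claimed at one-sided 0.05, which would itself need to be said.

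Second, a reader might infer that the trial's power is 70%. The article does not support that. The figure holds only if the true inputs are ones that make 85 per arm give 80%, and the margin of about 3.5 kg that would do so with a 1.6 kg deficit appears nowhere. The margin actually stated gives power near zero at either level, which is the larger defect in the paragraph. This objection stands, and the 70% must be read as conditional.

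Third, the baseline term may recover some power. That is correct, but by a few points in the range shown, and with no documented correlation.

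Fourth, a reader might infer that the mismatch inflates false non-inferiority claims. It does not: the interval rule is the stricter of the two levels.

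**Conclusion.** The point holds in conditional form. The article sizes Aim 1 at one-sided 0.05 and, on the conventional reading of a 95% interval, decides it at one-sided 0.025. For any inputs that make 85 per arm yield 80% power at the first level, power at the second is about 69 to 71% before baseline adjustment, and 80% would need about 107 to 110 evaluable per arm. This rests on SD 5 kg, equal arms, a two-sided interval and a distance to the margin of about 1.9 kg. It cannot be quoted as the trial's power while the 0.33 kg margin and the 1.6 kg deficit stand unreconciled. The consequence is overstated planning power and an ambiguous error rate on the primary outcome. It should be fixed, but it is secondary to the conflict between margin and assumed difference.

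**What to change.** In section 2.4.2, state that the interval is two-sided 95%. In section 2.4.2.2, set alpha to one-sided 0.025. Then reconcile the margin with the size and direction of the assumed difference, and only after that restate the power at 85 per arm: about 70% if the reconciled inputs reproduce the stated 80% at one-sided 0.05, otherwise whatever they give. If baseline adjustment is to be credited, state the assumed correlation.

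Alternatively, if one-sided 0.05 is what the sponsor intends for non-inferiority, state a 90% interval for that claim in section 2.4.2 and keep the 95% interval for superiority.

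Either route changes wording only. The cost of the first is a less favourable stated power, or a larger sample if 80% is to be kept; the cost of the second is an openly looser level for the non-inferiority claim.
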